### Study Procedures

All full-time therapists at both study sites who volunteer to participate will be consented. We project 4 therapists at each site (N=8) will participate. As in the authors’ previous work [79], clinic staff will discuss the research opportunity with the families of all the adolescents during routine intake procedures. If consent is given, clinic staff will send the family’s contact information to the study team through secure channels. The study team will contact interested caregivers by phone to complete (1) consent to phone screen, audio record sessions, complete outcome interviews and questionnaires, and grant access to clinic records and (2) an eligibility screener assessing IDs. IDs will be assessed using the Achenbach System of Empirically Based Assessment Child Behavior Checklist [122], a well-validated assessment method for screening for depression and anxiety problems in youth. IDs will also be assessed during the baseline research assessment using the Mini-International Neuropsychiatric Interview for Children and Adolescents [123,124], a structured diagnostic interview administered by lay interviewers; the interview yields Diagnostic and Statistical Manual of Mental Disorders, Fifth Edition, Text Revision categories and has been used in diverse adolescent samples [79,125]. Client data on protocol viability (limited to Fam-AID cases only) and clinical outcomes will then be collected on all study clients (regardless of amount of treatment participation) at baseline, 3-month, and 6-month follow-up using REDCap (Research Electronic Data Capture; Vanderbilt University) cloud software, a widely used and secure Health Insurance Portability and Accountability Act (HIPAA)–compliant, web-based data collection platform.

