### Study Measures

#### Fam-AID Fidelity Checklist

This study will use an adapted version of the Inventory of Therapy Techniques (ITT [95,96]), a postsession therapist-report fidelity tool that requires 1 or 2 minutes to complete. ITT items are designed to measure the extensiveness (ie, thoroughness and frequency) with which a given treatment technique was used on a 3-point Likert-type scale: 0 (not at all), 1 (a little bit or moderately), or 2 (quite a bit or extensively). ITT items are derived from treatment protocols and their associated observational fidelity tools, for example, for family therapy [51] and for CBT [67], after being vetted for relevance by community clinicians in multiple treatment settings [134]. ITT has shown strong construct [50,134] and predictive [79,135] validity in studies with adolescents receiving family therapy and CBT in usual care. The Fam-AID Fidelity Checklist mimics the ITT structure, containing multiple items in each of the 5 Fam-AID modules: culturally attuned family engagement, relational reframing of ID symptoms, functional analysis of ID symptoms, CBT treatment techniques for ID, and SUD+ID education and safety planning. The Fam-AID Fidelity Checklist–Observer Version is an identical measure with instructions for observer coding.

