*Aim 1 fidelity benchmarks* analyses (Fam-AID condition only) will examine both types of previously described fidelity metrics. Regarding coverage, descriptive statistics will capture frequencies related to (1) proportion of clients who received at least 1 intervention from each of the 5 modules and (2) interventions from which modules were most or least favored across clients. Chi-square analysis will be used to compare study conditions on the proportion of clients who received adequate coverage and conduct one-way analysis of variance to assess mean differences across modules in the Fam-AID condition to evaluate module preferences among therapists. Regarding dose, statistical equivalence testing [153] will be used to examine whether clinicians’ average scores for intervention extensiveness on both observer- and therapist-report versions of the Fam-AID Fidelity Checklist are equivalent to a designated benchmark, which will be set (granting appropriate latitude for a pilot trial) for each module as mean 2.5 (SD 0.50). A CI approach will be adopted in which an equivalence interval is defined as the benchmark +10% and –10%. Next, a CI is defined by the following formula: CI_90%_=M_R_–M_T_+/–z_α_(S_MR−MT_). In this equation MR represents the benchmark module mean, MT the average module score for study therapists, zα the critical one-tailed value from the z distribution for the chosen value of α, and SMR−MT the pooled SE. If the calculated CI falls within the equivalence interval, equivalence can be concluded. In addition, therapist variability in Fam-AID fidelity will be examined via statistical process control analyses (refer to the study by Hogue and Dauber [125]) in which individual therapist fidelity scores are plotted on a control chart to check for meaningful variation compared to control limits represented by the designated fidelity benchmark.

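### The formal equivalence rule for Aim 1 dose compares a CI for a difference with limits worded as raw scores, and its 2.5 benchmark lies above the 0–2 checklist scale

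*Protocol article*

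**What the plan says.** The rule is in the Aim 1 fidelity paragraph of the Plan of Analyses and has four parts.

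- **Benchmark.** It is set "for each module as mean 2.5 (SD 0.50").
- **Limits.** The text says that "an equivalence interval is defined as the benchmark +10% and –10" per cent.
- **Interval estimate.** A 90% CI is built as M_R − M_T plus or minus a z value times a pooled standard error, where "MR represents the benchmark module mean, MT the average module score for study therapists". The multiplier is "the critical one-tailed value from the z distribution for the chosen value of α".
- **Decision.** "If the calculated CI falls within the equivalence interval, equivalence can be concluded".

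The rule applies to the therapist-report and the observer-report checklists. The section on the Fam-AID Fidelity Checklist gives the parent instrument's item scores as "0 (not at all), 1 (a little bit or moderately), or 2 (quite a bit or extensively") and adds that "The Fam-AID Fidelity Checklist mimics the ITT structure".

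Dose is also defined in two other places. Specific Aims of the Study asks whether the average module extensiveness score exceeds the mean of the fidelity measure. Fam-AID Training and Fidelity Monitoring asks for a score at or above the scale mean on at least one technique per module, tracked for each case.

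**The concern.** In an equivalence test the margin and the CI must refer to the same quantity. Here the CI is for a difference, for which agreement means zero. The limits are worded as the benchmark itself plus and minus a tenth, for which agreement means 2.5. An analyst who follows the sentences as printed gets the wrong answer in both directions: agreement with the benchmark is rejected, and a score near the bottom of the scale can be accepted.

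Fidelity is one of the two components of Aim 1, and promising findings are meant to support a later randomized trial. The threshold should therefore be right before data are collected.

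**Working it through.** **Inputs from the protocol.** Benchmark M_R = 2.5 and SD 0.50; a 90% CI with a one-tailed z, hence z = 1.645 (Plan of Analyses). Item range 0 to 2, so the largest possible module mean is M_T = 2.0 (Fam-AID Fidelity Checklist). Thirty Fam-AID clients (Specific Aims). Eight therapists: "We project 4 therapists at each site (N=8) will participate" (Study Procedures). Three coded sessions per client (Study Procedures), hence up to 30 × 3 = 90 observer-coded sessions.

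**Assumptions.** The protocol gives no n and no worked standard error for this test, so there is no printed result to reproduce. I took SD 0.50 and n = 8, 30 or 90, with SE = SD/√n (one-sample) or SD × √(2/n) (two-sample pooled form). Observations are treated as independent.

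**Step 1: limits as worded.** 0.90 × 2.5 = 2.25 and 1.10 × 2.5 = 2.75.

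**Step 2: zero difference.** If M_T = M_R, the CI is 0 ± 1.645 × SE. It contains 0 whatever the SE, and 0 is outside 2.25 to 2.75. The rule fails at every sample size.

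**Step 3: what passes literally.** The lower CI limit must reach 2.25: 2.5 − M_T − 1.645 × SE ≥ 2.25, so M_T ≤ 0.25 − 1.645 × SE. The upper limit must not exceed 2.75, which for M_T ≥ 0 holds whenever 1.645 × SE ≤ 0.25.

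| n | SE form | SE | Half-width | Literal rule passes for |
|---|---|---|---|---|
| 8 | one-sample | 0.177 | 0.291 | no score |
| 8 | two-sample | 0.250 | 0.411 | no score |
| 30 | one-sample | 0.091 | 0.150 | M_T ≤ 0.10 |
| 30 | two-sample | 0.129 | 0.212 | M_T ≤ 0.04 |
| 90 | one-sample | 0.053 | 0.087 | M_T ≤ 0.16 |
| 90 | two-sample | 0.075 | 0.123 | M_T ≤ 0.13 |

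A module that is hardly delivered would probably show less spread than 0.50. With SD 0.10 and the one-sample SE, the bound is 0.25 − 0.030 = 0.22 at n = 30 and 0.25 − 0.058 = 0.19 at n = 8. The empty row at n = 8 therefore depends on SD 0.50. In no case does the pass region come near the benchmark.

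**Step 4: does an on-scale benchmark cure it?** Take 1.0 with SD 0.20 and n = 30, for illustration only. The limits are 0.90 to 1.10 and the half-width is 1.645 × 0.20/√30 = 0.060. An exact match still gives a CI around 0 and fails; only M_T ≤ 1.0 − 0.90 − 0.060 = 0.04 passes. The scale mismatch is separate from the choice of benchmark.

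**Step 5: does correcting the scale alone cure it?** On the difference scale the limits are −0.25 to +0.25. At n = 30, M_T would have to lie in 2.40 to 2.60 (one-sample) or 2.46 to 2.54 (two-sample). The checklist stops at 2.0, so the smallest possible difference is 2.5 − 2.0 = 0.5, which is more than 0.25. The rescaled rule cannot be met either.

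**The case against.** The strongest reply is that this is loose wording. The paragraph sets out to test equivalence to a benchmark and builds a CI for the difference from it, so the natural meaning of the ±10% is 0.25 either side of zero. On that reading the mismatch disappears. I think this is the likely intent. It does not clear the text, because the formula, its terms and the decision rule are all printed and nothing says that the limits are centred on zero. A CI for the therapists' mean against 2.25 to 2.75 would be an equally possible repair. This is a misstated threshold, not detail that a condensed article leaves out.

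Four stronger inferences should be resisted.

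- A reader might infer that this is the sole test of dose, so that an undelivered module would go through unnoticed. It is the only formal statistical test, but the two dose definitions against the scale mean would fail such a module, and the coverage analysis and the therapist control charts are further checks.
- A reader might infer that the study will in practice declare undelivered modules equivalent. That follows only from the literal reading, and an analyst would probably notice the mismatch on computing the first interval.
- A reader might take the near-zero pass region as a fixed figure. It rests on an assumed n, SD and SE form.
- A reader might infer that rescaling makes the rule usable. With the benchmark at 2.5 on a 0–2 checklist, it does not.

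The objection that a mean of 2.5 cannot be observed on a 0–2 scale is correct for the printed benchmark, but step 4 shows that the mismatch would survive a change of benchmark.

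**Conclusion.** The formal equivalence rule for dose is wrong as written. Its CI is on the difference scale and its limits are worded on the raw-score scale. Under the literal reading a zero difference fails at any standard error, which needs no assumption. Only a module mean near 0 could pass: at most 0.10 with SD 0.50, n = 30 and a one-sample SE, and no score with n = 8 at that SD.

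A second defect sits beside it. The 2.5 benchmark exceeds the checklist maximum of 2, so even the rescaled rule is unattainable. This takes the Fam-AID checklist to keep the parent instrument's 0–2 scoring, as its description indicates.

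The consequence is confined to one fidelity analysis in a pilot study. Aim 2 and its power calculation are unaffected.

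**What to change.** Restate the rule on one scale, in either of two ways:

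- compare the 90% CI for M_R − M_T with −0.10 × benchmark to +0.10 × benchmark; or
- compare the 90% CI for M_T with 0.90 × benchmark to 1.10 × benchmark.

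Then reconcile the benchmark with the checklist: either state a benchmark (and SD) that lies on the 0–2 scale, or correct the description of the scale if the Fam-AID version is scored differently. Check precision at the same time, because a margin of 10% shrinks with the benchmark. At 1.0, for example, it is 0.10, while the half-width at SD 0.50 and n = 30 is 0.150, so nothing could pass.

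The scale correction is one sentence. The benchmark needs a short decision and a matching edit. Neither needs new data or an extra analysis, and both can be settled before data collection, which the protocol plans to start in April 2025.

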### Specific Aims of the Study

In year 1, this study will develop a Fam-AID implementation toolkit during a three-part *pilot stage* at 1 pilot site by (1) soliciting provider input on Fam-AID components; (2) creating video-based training and fidelity procedures, leveraging the research team’s existing training and consultation resources in both core family-based interventions [75,76] and adolescent-focused transdiagnostic techniques [77] for adolescent behavior problems; and (3) piloting the toolkit with 4 to 6 clients. In years 2 to 3, this study will conduct an *interrupted time series* evaluation for 60 adolescent SUD+ID cases across 2 sites serving diverse clients: 30 cases will receive treatment as usual (TAU), and then following clinician training, 30 new cases will receive TAU enhanced by Fam-AID.

This protocol development study has 2 specific aims:

Aim 1 (protocol feasibility): in the Fam-AID condition only, the study will evaluate (1) protocol acceptability via client and therapist qualitative interviews and (2) fidelity benchmarks via therapist- and observer-report fidelity measures of protocol coverage (Is each module delivered in at least 1 session?) and protocol dose (Is the average module extensiveness score greater than the mean of the fidelity measure?).Aim 2 (protocol outcomes): in comparing the TAU only condition versus the TAU+Fam-AID condition, the study will examine the protocol’s impacts on (1) family member session attendance using clinic logs and (2) adolescent ID-related symptoms (emotion regulation, depression, and anxiety), SU, and family communication about SUD+ID at 3-month and 6-month follow-up. Overall, these pilot-scale protocol viability and impact findings, if promising, will set the stage for a randomized trial to examine the effects of Fam-AID on immediate and ultimate outcomes in a larger community sample.

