### Fam-AID Training and Fidelity Monitoring

Site clinicians will be trained for 6 hours. The session will feature video-based training [117,118] in Fam-AID modules and techniques. Thereafter, consultation at each site will include bimonthly live consultation with a protocol expert focused on equipoise between protocol fidelity and case tailoring, along with continuous feedback from therapist- and observer-report fidelity data, which is emailed directly to clinicians and used in live consultation to enable rapid adjustment in protocol delivery [119-121]. Two main fidelity benchmarks will be monitored for each case. These benchmarks include clinicians delivering interventions for every module in at least 1 treatment session (ie, coverage) and clinicians performing at or above the mean scale score for intervention extensiveness on the Fam-AID Fidelity Checklist (described in the Study Measures section) for at least 1 technique from each module (ie, dose), with both therapist- and observer-report checklist versions being tracked.

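### The dose fidelity benchmark is stated as at or above the scale mean, but it is tested with a two-sided equivalence rule that does not test that criterion

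*Protocol article*

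**What the plan says.** Three sections of the protocol article describe the dose benchmark.

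- **Specific Aims of the Study** puts it as a question: "Is the average module extensiveness score greater than the mean of the fidelity measure".
- **Fam-AID Training and Fidelity Monitoring** describes it as "clinicians performing at or above the mean scale score for intervention extensiveness on the Fam-AID Fidelity Checklist", for at least one technique from each module.
- **Plan of Analyses** (Aim 1 fidelity benchmarks) says it examines the metrics already described, and then chooses a different kind of test: "Regarding dose, statistical equivalence testing [153] will be used to examine whether clinicians’ average scores for intervention extensiveness" are equivalent to a designated benchmark. The benchmark is set "for each module as mean 2.5 (SD 0.50"). The margin is given as follows: "an equivalence interval is defined as the benchmark +10% and –10" percent. A 90% CI is formed for the benchmark mean minus the therapist mean, using a one-tailed z value and a pooled SE. The decision rule is "If the calculated CI falls within the equivalence interval, equivalence can be concluded".

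The checklist itself (Study Measures, Fam-AID Fidelity Checklist) is scored 0, 1 or 2.

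**The concern.** An equivalence test asks whether a mean is close to a reference value in both directions. The aims and monitoring sections ask whether it reaches or exceeds the reference. The two questions agree on a module delivered well below the benchmark. They disagree on a module delivered well above it, which meets the stated criterion but fails the printed rule.

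No section sets an upper limit on desirable extensiveness, and none says that exceeding the upper equivalence limit counts as meeting the benchmark. The rule is printed with its formula and margin, so this is a stated choice and not a detail left to a later document.

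Dose is one of the two fidelity benchmarks in Aim 1, and the article says that promising pilot findings will set the stage for a randomized trial. A rule that cannot recognise strong delivery would misinform that step.

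**Working it through.** The article states no power or error rate for this test, so there is no figure to reproduce. The printed rule was applied directly.

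**Inputs from the article.** Benchmark M_R = 2.5 and SD 0.50; margin 10% of M_R; 90% CI with one-tailed z = 1.645; checklist range 0 to 2; 30 Fam-AID clients; 8 projected therapists.

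**Assumptions.** The article does not fix the unit of analysis or the exact SE. The main case uses 30 independent client scores, SD 0.50 and SE = SD/√n. Variations follow.

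**Rule.** Equivalence is concluded if (M_R − M_T) ± 1.645 × SE lies within ± 0.10 × M_R.

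**1. As printed.** The margin is 0.10 × 2.5 = 0.25, so the limits are 2.25 and 2.75. The highest possible mean is 2.0, which gives M_R − M_T = 0.5. That exceeds 0.25, so perfect scores fail on the low side at any sample size and the upper limit is never reached.

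**2. Benchmark moved to the 0 to 2 midpoint, for illustration.** With M_R = 1.0 the margin is 0.10 and the limits are 0.90 and 1.10. An observed mean of 2.0 gives a difference of −1.0. The centre of the CI is already outside the limits, so this fails at any sample size.

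**3. Benchmark kept at 2.5 on a longer scale, for illustration.** SE = 0.50/√30 = 0.0913 and the half-width is 1.645 × 0.0913 = 0.150. Equivalence needs an observed mean within 0.25 − 0.150 = 0.100 of 2.5, so means above about 2.60 fail. With d = true mean − 2.5, the pass rate is Φ((0.100 − d)/0.0913) − Φ((−0.100 − d)/0.0913). The comparison column uses only the low-side limit: the lower limit must exceed 2.25, so the pass rate is Φ((d + 0.100)/0.0913).

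| True mean | Printed two-sided rule | Low-side limit only |
|---|---|---|
| 2.25 | 0.05 | 0.05 |
| 2.50 | 0.73 | 0.86 |
| 2.625 | 0.38 | 0.99 |
| 2.75 | 0.05 | 1.00 |
| 3.00 | 0.00 | 1.00 |

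The printed rule treats a module 10% above the benchmark exactly like one 10% below it.

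**4. Sensitivity to the unit and SE.**

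- Pooled SE with equal n: 0.50 × √(2/30) = 0.129, half-width 0.212, leaving 0.25 − 0.212 = 0.038. If the benchmark is a constant, the observed mean still varies with SE 0.0913. The pass rate is then 0.32 at 2.50 and 0.01 at 2.75.
- Eight therapist means: 1.645 × 0.50/√8 = 0.291, which exceeds 0.25, so equivalence could not be concluded at any true mean.
- Margin 0.10 (benchmark 1.0): the half-width of 0.150 for 30 clients exceeds it. Taking 90 coded sessions (3 for each of 30 clients) as independent gives 1.645 × 0.50/√90 = 0.087, just inside 0.10. The pooled version, 0.123, does not fit. Treating sessions as independent ignores clustering.

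**The case against.** The strongest objection is that, as printed, the upper limit does no harm. No score on a 0 to 2 checklist can exceed 2.5, so nothing better than the benchmark can be penalised. That is correct. A reader might infer that the current plan already scores the best delivery as failure because it is too good. The document does not support this: as printed, the best delivery fails for falling short of 2.25. The high-side problem appears only after benchmark and scale are reconciled. It still needs fixing at the same time, because correcting only the number would bring it into play.

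A second objection is that failing to conclude equivalence is not the same as failing the benchmark. The article does not use the word failure, a reported CI would show a module lying above the benchmark, and control charts are also planned. This stands in part. However, equivalence is the only module-level dose criterion in the Plan of Analyses, and the charts address variation between therapists. No go/no-go decision is tied to the result, which limits the severity.

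A reader might also infer that equivalence could never be shown with a benchmark of 1.0. That depends on a unit and an SD that the article does not fix, as the 90-session case shows.

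Two further details are minor. Comparing a CI for a difference with an interval around the benchmark is probably condensed wording for ± 10% on the difference. The choice of z over t matters mainly if 8 therapist means are the unit: the half-width would be 1.895 × 0.177 = 0.335 with t on 7 degrees of freedom, against 0.291 with z. The pooled SE follows a cited method that is not shown, but it needs clarifying because a designated benchmark has no sampling error.

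**Conclusion.** The concern holds in a limited form, and the point should be fixed. The two-sided rule does not test the one-directional dose criterion in the aims and monitoring sections, and no section reconciles them.

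The mismatch in direction needs no assumptions, and neither does the failure of perfect scores under the printed 2.5. Failure of a mean of 2.0 at any sample size assumes only that the benchmark becomes 1.0 with the 10% margin kept. The pass rates of 0.73 at 2.50 and 0.05 at 2.75 assume a longer scale, SD 0.50, 30 independent client scores and SE = SD/√n. Other choices of SE and unit change these rates, but the rule remains symmetric about the benchmark.

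**What to change.** Reconcile the three sections and the checklist on the benchmark value, its direction and its unit (module average, or at least one technique per module). Then replace the equivalence rule with a one-sided one:

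- A module meets the dose benchmark if the lower one-sided 95% confidence limit of its mean is at or above the benchmark. If some shortfall is acceptable, the limit must instead lie above the benchmark minus a stated margin.
- Justify any margin on the reconciled scale. The 0.25 points should not be carried over from 2.5. With a benchmark of 1.0 and the assumptions above, a module truly at 0.95 would pass if its observed mean exceeded 0.75 + 0.150 = 0.900, which has probability Φ((0.95 − 0.900)/0.0913) = 0.71.
- Treat the benchmark as a constant and take the SE from the study data, allowing for clustering by therapist.

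The text change is about one paragraph, and recruitment is not due to begin until April 2025. The real cost is precision. With about 8 therapists the lower limit will be imprecise, and with no margin a module exactly at the benchmark passes only about 5% of the time. The point estimate and CI for each module should therefore be reported alongside the rule.

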**Methods:**

This quasi-experimental study will proceed in 2 stages. The pilot stage will use rapid-cycle prototyping methods in collaboration with end-user stakeholders to draft protocol delivery and fidelity guidelines adapted from existing resources, solicit provider and client input on protocol content and delivery via cognitive interviewing, and pilot prototype components on 4 to 6 cases. The second stage will be an interrupted time series study for 60 comorbid SUD+ID cases across 2 sites serving diverse adolescents: 30 will receive treatment as usual (TAU); following clinician training in the protocol, 30 new cases will receive TAU enhanced by Fam-AID. For aim 1, the focus is on evaluating the acceptability of the Fam-AID protocol through therapist and client interviews as well as assessing fidelity benchmarks using therapist- and observer-reported protocol fidelity data. For aim 2, the plan is to compare the effects of TAU only cases versus TAU+Fam-AID cases on family treatment attendance and on adolescent ID and substance use symptoms, with measurements taken at baseline and at 3-month and 6-month follow-ups.

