### Interrupted Time Series: Study Design

Following the completion of the pilot stage, the team will conduct an interrupted time series study featuring quasi-experimental pilot effectiveness research methods to evaluate the Fam-AID protocol and implementation toolkit [87]. Figure 2 depicts the basic design and timeline of the interrupted times series study. The quasi-experimental interrupted time series with nonequivalent groups, which tracks target data both before and after introducing a programmatic change to a group whose membership may vary over time, is appropriate for testing viability and impacts of new interventions delivered in field settings [88-90]. This design is functionally similar to a posttest-only design with a nonequivalent historical control group. Two partner clinic sites will be involved to reduce confounds from site-specific implementation effects and increase diversity in clients and therapists. Aim 1 methods will feature procedures designed for stage 1 treatment development [91,92] to establish proof-of-concept (acceptability and fidelity benchmarks) for the protocol and toolkit. Aim 2 methods will examine Fam-AID’s impact on family member attendance in treatment and client outcomes (adolescent ID symptoms, adolescent SU, and parent-adolescent communication about SUD+ID).

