*Aim 2a family attendance* will involve between-condition comparison of treatment sessions attended by family members other than the adolescent. Linear mixed effects (LME) modeling will be used to examine the effect of condition on attendance counts. The model will include fixed effects for independent variables (ie, condition) and random effects to account for nesting at the therapist level, thereby providing unbiased parameter estimates [154,155]. Nesting at the client level will not need to be controlled in these analyses, as client summed totals will serve as a dependent measure: tallies of sessions attended by family members will be summed across the follow-up period. The LME models package [156] will be used; it provides full information maximum likelihood estimation and restricted maximum likelihood estimation, both of which produce unbiased parameter estimates based on the assumption that data are missing at random and outperform other missing data approaches even when missing at random is not met [157]. Effect sizes will be indexed by η_2_ [158]. However, the nonlinear mixed effects model will be used if the assumption of continuous data is not tenable (eg, when attendance counts are not normally distributed).

*Aim 2b adolescent and family outcomes* analyses will involve similar LME models previously described. To test for change over time, each model will include fixed effects for time (months since baseline, coded as 0, 3, and 6) and random effects for (1) nesting of clients within therapists and (2) repeated measures within person across follow-up. Hypotheses will be tested by adding condition as a fixed effect and examining the condition-by-time interaction on each outcome in separate models. Acknowledging that outcomes may not demonstrate sharp trajectory change during the relatively brief 6-month follow-up window, the intercept will be set at the terminal assessment point by recoding time points (–6, –3, and 0); in doing so, the condition effect for the intercept will reflect a between-group difference at 6-month follow-up. LME modeling is recommended as an alternative to traditional modeling techniques for longitudinal designs with small samples [159].

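### Aim 2 compares consecutive non-randomized cohorts without adjusting for site or baseline case mix, which leaves the attendance comparison and the 6-month contrast open to bias

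*Protocol article*

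**What the plan says.** The abstract sets out two consecutive cohorts: "30 will receive treatment as usual (TAU); following clinician training in the protocol, 30 new cases will receive TAU enhanced by Fam-AID". The section Interrupted Time Series: Study Design describes nonequivalent groups and a programmatic change introduced "to a group whose membership may vary over time". It also says: "This design is functionally similar to a posttest-only design with a nonequivalent historical control group". On the sites it says: "Two partner clinic sites will be involved to reduce confounds from site-specific implementation effects".

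The Plan of Analyses then fixes the models.

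- **Aim 2a (family attendance, one summed count per client):** "The model will include fixed effects for independent variables (ie, condition) and random effects to account for nesting at the therapist level". The same sentence goes on to claim unbiased parameter estimates as the consequence.
- **Aim 2b (symptoms, substance use, communication):** similar models with time at 0, 3 and 6 months and random effects for therapist and person. "Hypotheses will be tested by adding condition as a fixed effect and examining the condition-by-time interaction on each outcome in separate models". Time is also recoded so that "the condition effect for the intercept will reflect a between-group difference at 6-month follow-up".

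No model names site or any baseline client characteristic. Study Design Limitations and Strengths concedes that randomization controls unknown confounds better, but states no adjustment in its place.

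**The concern.** Condition coincides with period, and the clients differ between periods. Any change in who is enrolled, or in how much each site contributes, can therefore appear as a condition effect unless the model accounts for it. For Aim 2a the parenthesis after independent variables names condition alone, so this is a stated model and not a detail left open.

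A shift is plausible. Under Study Procedures, clinic staff introduce the study at intake. In the second period this happens at sites whose clinicians have just been trained in family engagement, and family attendance is the Aim 2a outcome.

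The unbiasedness claim does not follow from the model. A therapist random effect addresses correlation among clients of one therapist, not differences between clients treated before and after training. At stake is the study's between-condition evidence on outcomes, which is meant to support a larger trial.

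**Working it through.** **Inputs from the document:** 30 + 30 clients; 2 sites; 8 projected therapists (4 per site), so 60/8 = 7.5 clients each; 3 occasions with r = 0.50; alpha .05; planned d = 0.60 (Study Power).

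**Assumed, because the document gives no figure:** site gap, site shares per period, severity shift, its correlation with the outcome, and therapist variance.

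**1. The plan's own power figure.** For an effect averaged over 3 occasions, SD = sqrt((1 + 2 x 0.5)/3) = 0.816 and SE = 0.816 x sqrt(2/30) = 0.211. At d = 0.60, 0.60/0.211 = 2.85, and two-sided power is 0.81 (normal) or 0.80 (t, 58 df). At d = 0.50 it is 0.66 or 0.65. The stated 0.80 and 0.65 reproduce, and this point does not change them; d = 0.60 serves only as the yardstick.

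**2. Site-mix shift.** Crude bias = site gap x change in site share.

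- Gap 0.5 SD, one site supplying 20/30 TAU and 10/30 Fam-AID cases: 0.5 x 10/30 = 0.167 SD.
- Fraction absorbed by the therapist intercept, to a first approximation: n x tau² / (n x tau² + residual variance). With tau² = 0.0625 (0.25², what a 0.5 SD site gap itself creates), 7.5 x 0.0625 = 0.469, and 0.469/(0.469 + 0.9375) = 0.33.
- Remaining bias: 0.167 x (1 - 0.33) = 0.11 SD, or 0.111/0.60 = 19% of the planned effect.

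This assumes that therapists carry cases in both periods.

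**3. Severity shift, Aim 2a.** Bias = shift x correlation with the outcome.

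- 0.3 x 0.5 = 0.15 SD and 0.5 x 0.5 = 0.25 SD.
- With SE of about sqrt(2/30) = 0.258, 0.15/0.258 = 0.58 and 0.25/0.258 = 0.97. The chance of |Z| > 1.96 is then about 0.09 and 0.16.

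**4. Simulation.** True effect 0, 3000 runs per scenario, REML with a random therapist intercept, therapist ICC 0.05. Type I error is in brackets.

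| Assumed scenario | Crude bias | Bias, condition only | Bias, site + baseline covariate added |
|---|---|---|---|
| Site gap 0.5 SD, share 50% to 70% | 0.10 | 0.065 (0.059) | 0.006 (0.053) |
| Site gap 0.8 SD, share 40% to 70% | 0.24 | 0.097 (0.072) | 0.000 (0.050) |
| Site gap 0.8 SD, share 30% to 70% | 0.32 | 0.151 (0.094) | 0.007 (0.051) |
| Severity shift 0.3 SD | 0.15 | 0.151 (0.090) | 0.004 (0.050) |
| Severity shift 0.5 SD | 0.25 | 0.247 (0.163) | -0.004 (0.051) |
| Gap 0.8 SD, 30% to 70%, and shift 0.5 SD | 0.57 | 0.397 (0.316) | 0.005 (0.051) |

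The therapist effect absorbs roughly 35 to 60% of a site shift (0.065/0.10 remains in the first row, 0.097/0.24 in the second). It absorbs essentially none of a severity shift.

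**5. Aim 2b.** Take a 0.3 SD baseline difference and fit a straight line over -6, -3 and 0.

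- Persistent (0.3, 0.3, 0.3): slope 0, so interaction bias is 0; the 6-month intercept is biased by 0.30.
- Partly regressing (0.3, 0.15, 0.15): slope = (-3 x 0.3 + 3 x 0.15)/18 = -0.025 per month, or -0.15 over 6 months. Intercept at month 6 = 0.20 - 3 x 0.025 = 0.125.

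**The case against.** The strongest reply has five parts.

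- **The model removes something.** A reader might infer that it leaves all the confounding in place. It does not. Therapists are consented as one group and all staff are trained after the TAU period, so the therapist term can take up part of a site difference. A stable baseline difference drops out of the condition-by-time interaction, which is the stated hypothesis test for Aim 2b. This stands.
- **The site bias is modest.** A reader might set the crude 0.167 SD against d = 0.60 and report 28%. That ignores the absorption; 19% is nearer under the same assumptions. The gap and shares are themselves assumed. Figure 2 and the full protocol are not shown, so one cannot say that no per-site enrolment target exists. With equal shares in both periods this component vanishes. This stands too, and makes severity the larger concern.
- **The text on sites is no promise.** Using two clinics to avoid dependence on one is a design reason, not a commitment to adjust for site. There is no contradiction with the model.
- **The design is already disclosed.** A reader might infer that the interrupted time series label hides a before/after comparison. The document says openly that it works like a historical-control design. This stands, but disclosure does not adjust the estimate.
- **Covariates may be left to an analysis plan.** That would answer silence. Here the article names condition as the fixed effect and claims unbiasedness for the result, so the text needs correcting whatever another document adds.

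**Conclusion.** The point holds with limits. Followed as written, the Aim 2a comparison and the Aim 2b 6-month contrast pass between-period differences in client severity, and part of any difference in site mix, into the condition effect.

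Under the assumed values the bias is about 0.11 SD for a large site-mix change and 0.15 to 0.25 SD for a 0.3 to 0.5 SD severity shift. In the latter case type I error is about 0.09 to 0.16 instead of 0.05. The SD-unit figures treat the outcome as roughly continuous.

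The documents do not support saying that every Aim 2 result is affected alike. The interaction is protected when the baseline difference is stable, though not when it regresses (-0.15 SD in the example). Adjustment corrects measured differences only; calendar period remains confounded with condition in this design.

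**What to change.** 1. Add site as a fixed effect in all Aim 2 models.
2. In Aim 2a, also add a short prespecified baseline set already collected, for example age, sex, baseline RCADS total and baseline CRAFFT.
3. In Aim 2b, choose in advance between two routes. Either model months 3 and 6 only, with the outcome's own baseline as covariate, and read the contrast at month 6; or rely on the condition-by-time interaction. The two rest on different assumptions in nonequivalent groups and need not agree.
4. Do not enter an outcome's month-0 value as both response and covariate. In a small simulation without therapist or site terms (300 runs, no true effect), doing so raised type I error for the 6-month contrast from 0.05 to about 0.10. With a regressing 0.3 SD baseline difference it turned the bias from +0.11 to -0.07.
5. Drop the claim that the therapist random effect makes the estimates unbiased. State that calendar period stays confounded with condition, in line with the historical-control description already given. An enrolment-date covariate would not solve this, because date nearly determines condition. A per-site quota is not needed.

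The cost is 1 degree of freedom for site and up to about 5 in Aim 2a (site plus four covariates, leaving about 53 of 58). No new data are needed. Recruitment is planned for April 2025, after the article's publication, so the change can be fixed before data exist.
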